**Fig. 3 Fig3:**
[figure not shown]
Flow diagram

### Eligibility criteria and randomization

The criteria for *gott*-level eligibility were (1) the lowest coverage of improved sanitation, (2) the lowest coverage of improved water, (3) similar population size, (4) similar distance from the main road, (5) road accessibility, (6) sufficient number of households with an under-five child, (7) sufficient distance between study *gotts* to prevent contamination, and (8) no other WaSH projects are to be implemented during the study period.

To select eligible *gotts* for the study, we used the data from the preliminary survey and from the special survey for the water pipe connection. The preliminary survey was carried out in March through May 2013, and the special survey was conducted in August 2014 in 212 *gotts* across the two target districts.

The criteria for household level eligibility are (1) having a child under 60 months at the time of recruitment and (2) agreeing to register with informed consent.

The age of a child will be verified with an immunization card, which shows the birth date of the child. Informed consent from 1200 households registered will be obtained from the mother or caregiver in written form. A structured questionnaire will be administered regarding water, sanitation, and hygiene, including demographics and socioeconomic characteristics.

The *gotts* in the study area were stratified according to the administrative unit (*kebelle*, in Amharic, which is the administrative unit above the *gott*) so that every *kebelle* contained both intervention and control *gotts*. By doing so, we were able to increase the balance between the intervention and control arms because *gotts* in the same *kebelle* were expected to have more common characteristics in terms of economic status, tribe, religion, geographical conditions such as altitude, and WaSH-related behaviors. In addition, local government officials of the study area also requested that we allocate the same number of study *gotts* in each *kebelle* to prevent any conflicts of interest among the *kebelles*. To avoid contamination, we allocated a buffer zone between the intervention and control *gotts* in every *kebelle*. A closed cohort design will be employed for the study. Any new baby born during the longitudinal survey period will not enrolled for the study.

### Intervention

In alignment with the National Hygiene and Sanitation Strategic Action Plan (2011-2015) [18], the Ethiopian Government’s policy on sanitation, we applied the principles of Community-Led Total Sanitation (CLTS) for the study. The Gurage zonal office, the SNNPR State of Ethiopia, and the Re-shaping Development Institute (ReDI) are implementing the project. The project is funded by the Korea International Cooperation Agency (KOICA).

### CLTS implementation

In accordance with the Ethiopian government’s guidelines on this issue, the primary approach for implementation of latrine improvement and hygiene promotion adopted for this program is Community-Led Total Sanitation. Of 48 *gotts* selected in the project area, 24 *gotts* in the project area were selected (intervention arm) and will receive the CLTS intervention and undergo intensive follow-up throughout the first phase of the implementation period (approximately 12 months) for latrine improvement. As the first step of CLTS, a team of trained CLTS facilitators will conduct the triggering process in each of these 24 *gotts*. During this triggering process, facilitators will use participatory tools, such as transect walk, sanitation mapping, and calculating feces deposition to help community members realize the health effects of open defecation practices in their *gotts*. In the process, basic human emotions, including shame and disgust, will be aroused among the *gott* members regarding their own defecation practices. Successfully implemented, the triggering activities of the CLTS, which normally take half a day for each *gott*, can be a very effective tool to motivate community members to stop open defecation and to eventually construct and use latrines of their own accord.

In accordance with the core principle of CLTS, no material or financial subsidies will be provided for the construction of individual household latrines. Household members will take responsibility for the whole process of latrine construction including (1) pit-hole digging; (2) constructing a slab and pit-hole cover; (3) constructing the walls, door, and roof; and (4) installing hand-washing facilities. The community member’s labor cost for construction of a latrine is expected to be approximately US$5.95 (125 Ethiopian birr as of October 23, 2015) per household. Ten full days of labor are estimated to be required for the construction of an improved latrine per household if two adults were to work together for the procurement of materials (wood, thatch, stone, and so on) and construction of the latrines.

We produced an operational definition for an improved latrine for the project as having (1) a pit-hole with at least 2.5 m of depth, (2) a slab, (3) a pit-hole cover, (4) a superstructure, (5) a door, (6) a roof, and (7) hand-washing facilities (Fig. 4). We did not prescribe the materials for any component of the latrine, expecting those to be locally available and affordable materials to ensure sustainability. If a latrine lacks any of the elements specified above, it would not qualify as an improved latrine.

**Fig. 4 Fig4:**
[figure not shown]
Model latrine

### WaSH promoter

At the beginning of the implementation period, one (1) villager from each intervention *gott* will be designated and trained as a WaSH promoter to carry out post-triggering or follow-up CLTS activities in his/her *gott*. To ensure the coverage and quality construction of the latrines in each *gott*, and also the long-term utilization of the latrines to be built, these WaSH promoters will employ a combination of various approaches including technical advice on latrine construction, collective awareness-raising, and household visits.

For this purpose, during the initial phase of implementation, WaSH promoters in each *gott* will be trained on key issues regarding latrine construction and use. Once trained, these WaSH promoters are to be the leading agents to promote and follow-up on the latrine improvement and sanitation-related behavior change in the promoter’s respective Gott. More specifically, WaSH promoters will be responsible for activities including household visits, community conversations, technical advice on latrine design, organization of and participation in monthly review meetings with stakeholders, and so on. In line with the Ethiopian government’s CLTS Guideline, no material subsidies will be provided for the construction of individual household latrines. Instead, most of the resources, both human and financial, of the project are to be allocated for activities aimed at promotion of latrine construction and use, as well as the sanitation behavior change of the community.

### Water intervention

When the CLTS intervention is completed, the second phase starts, during which water pipes will be connected to 24 *gotts* from one single spring on a mountain in each district. A spring capable of supplying sufficient water across the district is already identified and designing a water-pipe connection plan is under process. Immediately after the final round of the survey is finished, the water pipe will be connected to all the other 24 *gotts*.

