**Method/design:**

A phase-in and factorial design will be used for the study. The intervention for improving latrines will be implemented in an intervention arm during the first phase, and the comparable intervention will be performed in the control arm during the second phase. During the second phase, a water pipe will be connected to the *gotts* (villages) in the intervention arm. After the second phase is completed, the control group will undergo the intervention of receiving a water pipe connection. For diarrheal prevalence, five rounds of surveying will be conducted at the household level. The first four rounds will be carried out in the first phase to explore the effect of improved latrines, and the last one, in the second phase to examine the combined effects of improved water and sanitation. For documentation of diarrheal incidence and duration, the mother or caregiver will record the diarrheal episodes of her youngest child on the “Sanitation Calendar” every day. Of 212 *gotts* in the project area, 48 *gotts* were selected for the trial, and 1200 households with a child under 5 will be registered for the intervention or control arm. Informed consent from 1200 households will be obtained from the mother or caregiver in written form.

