### Study design

The study was approved by the National Research Ethics Review Committee under the Ministry of Science and Technology, Federal Democratic Republic of Ethiopia (NRERC 3.10/032/2015; July 29, 2015) and was registered as an ISRCT on March 13, 2015 (ISRCTN82492848).

In the study, a *gott*, the Amharic word for village, was taken as the randomization unit because we expected that improved latrines could impact diarrheal transmission across households within a *gott*, where people interact with one another most closely. All the interventions related to latrine improvement will be performed at each *gott* level.

A phase-in and factorial design will be used for the study. The intervention for improving latrines will be implemented in the intervention arm during the first phase, and the comparable intervention will be performed in the control arm during the second phase. During the second phase, a water pipe will be connected to the *gotts* in the intervention arm. After the second phase is completed, the control group will receive the intervention of a water pipe connection. With the design, we will investigate not only the effect of improved sanitation but also the combined effects of improved water and sanitation interventions.

A preliminary survey was carried out to develop this water, sanitation, and hygiene (WaSH) project intervention design in March to May 2013. Water pipes will be connected to 212 *gotts*, of which, 48 *gotts* were selected as the study area of the trial. In the intervention *gotts*, the procedures of the Community-Led Total Sanitation including pre-triggering, triggering, and follow-up will be carried out for latrine improvement beginning in November 2015 and will continue to October 2016.

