### Primary endpoint

The primary endpoint of the study is diarrheal prevalence in children under 5 years of age. We will use 7-day prevalence of reported diarrhea in the household, which will be based on parental reports. The survey will be conducted five times at the household level: the first four rounds will be carried out in the first phase to explore the effect of improved latrines, and the last one, in the second phase to assess the combined effects of improved water and sanitation.

In addition to diarrheal prevalence, we will measure diarrheal incidence and diarrheal duration. For documentation of diarrheal incidence and duration, we will have the mother or caregiver record the diarrheal episodes of her youngest child on a “Sanitation Calendar” (Amharic language: *Yenezehenna Gize Saleda*) on a daily basis (Fig. 2).

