### Health outcome assessment with a sanitation calendar

We distributed a sanitation calendar to all registered households beginning in December 2015 and asked mothers or caregivers to mark “O” or “X” depending on the presence of diarrheal disease of her youngest child every day over the 12-month period of longitudinal observation from December 2015 to November 2016. WaSH promoters have been monitoring the recording status of the sanitation calendar on a weekly basis and continue to educate and encourage mothers or caregivers to continue recording appropriately.

We devised an incentive mechanism to encourage the mothers or caregivers to record diarrheal episodes on the sanitation calendar properly by establishing a system where a well-maintained calendar can be used as a voucher. A well-recorded calendar, regardless of whether it contains Os or Xs will be exchanged with a gift-in-kind, probably sanitation-related materials such as soaps, nail clippers, toothpastes, or the like. WaSH promoters will take a photo of the sanitation calendar using a mobile phone and submit to a supervisor and the team leader. For the study, diarrhea is defined as three or more watery stools in 24 hours according to the WHO definition.

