### Intermediate outcomes

#### Sanitary survey

In each of the five rounds of the household survey (October 2015; March, July and November 2016; and July 2017), the presence of feces both inside and outside the household compound, and within the *gott* will be observed. The practices of child feces disposal will also be assessed by administering a structured questionnaire and observation.

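### Survey round 4 and the last calendar month are dated November 2016, but the stated rule lets phase 2 open once CLTS ends in October 2016, so phase-1 outcome data may be collected after phase 2 has begun

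*Protocol article*

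**What the plan says.** All references are to the Protocol article.

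- **End of phase 1.** Under Study design, the CLTS procedures in the intervention gotts "will be carried out for latrine improvement beginning in November 2015 and will continue to October 2016". CLTS implementation describes intensive follow-up of these 24 gotts "throughout the first phase of the implementation period (approximately 12 months) for latrine improvement".
- **Start of phase 2.** Water intervention gives an event and no date: "When the CLTS intervention is completed, the second phase starts, during which water pipes will be connected".
- **Content of phase 2.** The intervention gotts receive piped water. For latrines, the abstract and Study design say that "the comparable intervention will be performed in the control arm during the second phase".
- **Prevalence rounds.** Primary endpoint says that "the first four rounds will be carried out in the first phase to explore the effect of improved latrines". Sanitary survey dates the five household rounds: "October 2015; March, July and November 2016; and July 2017". Round 4 is therefore in November 2016.
- **Daily calendar.** Incidence and duration come from a calendar kept "over the 12-month period of longitudinal observation from December 2015 to November 2016".
- **Protection of the last round.** Water intervention makes the control gotts' water connection wait for the end of the final survey round. No corresponding sentence makes phase 2 wait for round 4 or for the last calendar sheet.

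**The concern.** Round 4 is placed in phase 1 in order to measure the effect of latrines alone. On the printed dates it follows the event that opens phase 2, and so does the last calendar month.

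The order matters because phase 2 changes exposure in both arms. CLTS started early in control gotts would shrink the latrine contrast. Water connected early in intervention gotts would add any water effect to it. If both interventions protect, the two errors have opposite signs, so the net error cannot be signed or corrected later unless the starting dates are recorded.

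Round 4 is also the phase-1 round with the longest exposure. It is the best opportunity to address the aim given in the Background, which is the effect once latrine coverage reaches a threshold.

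**Working it through.** **1. Month counts (inclusive).**
- CLTS, November 2015 to October 2016: 12 months. This reproduces the roughly 12 months given for the first phase.
- Calendar, December 2015 to November 2016: 12 months. This reproduces the stated length.
- Both durations are right, but the calendar window lies one month later than the CLTS window.

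**2. Size of the overlap.** If CLTS is completed by 31 October 2016 and phase 2 opens at once, round 4 falls 1 to 30 days after the opening. It is one of three post-baseline rounds in phase 1. For the calendar, 1 December 2015 to 30 November 2016 is 366 days, and November is 30/366 = 8.2 % of them.

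**3. Effect on the prevalence difference.** The inputs from Sample size calculation are a control prevalence of 24 % and a 30 % relative reduction.
- Planned: 0.24 × (1 − 0.30) = 0.168, so the difference is 0.24 − 0.168 = 0.072, or 7.2 points.
- Let f be the share of the full effect already gained by control gotts at round 4. The documents give no value; f = 0.10 is my assumption.
- Control prevalence at round 4: 0.24 × (1 − 0.30 × 0.10) = 0.2328.
- Round-4 difference: 0.2328 − 0.168 = 0.0648, about 6.5 points.
- Unweighted average over the three post-baseline rounds: (7.2 + 7.2 + 6.48)/3 = 6.96, about 7.0 points.

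**4. Effect on the incidence sample size.** The plan assumes 24 weeks for 25 children, or 600 child-weeks per gott. I take its k = 0.213422 and its rates 0.18 and 0.1422 as given, and use:

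c = 1 + (1.96 + z_β)² × [(0.18 + 0.1422)/y + k²(0.18² + 0.1422²)] / (0.18 − 0.1422)²

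- With y = 600 and z_β = 1.28 (the value in the text for 90 % power; the printed formula shows 0.28), c = 22.55, which is the plan's figure.
- The calendar gives (366 − 30)/7 = 48.0 weeks before November, twice the assumed 24. With y = 25 × 48 = 1,200, c = 20.58.
- With the whole calendar, y = 25 × 52.29 = 1,307.25 and c = 20.42.

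Omitting November everywhere would raise the requirement from 20.42 to 20.58 gotts per arm. That stays below the plan's 22.55 and the 24 available.

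**The case against.** A consistent reading is available. The first phase is only approximately 12 months long, two sections expressly assign the first four rounds to it, and an endline survey just after a year of CLTS, with phase 2 following, would be ordinary practice. No control-gott triggering or pipe connection is dated to November 2016. With 7-day recall, interviews in the first week of November partly cover October. The article condenses a fuller protocol, which may hold the field schedule.

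Fast contamination is also hard to credit. The pipe plan was still being designed. The half day quoted for CLTS covers triggering only; promoter training and follow-up come in addition. The ten days per latrine are labour for one household, and the plan itself allows about a year to build coverage.

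Much of this stands. A reader might infer that control gotts would gain 25 % or 50 % of the full effect, which would cut the round-4 difference to 0.75 × 7.2 = 5.4 or 0.50 × 7.2 = 3.6 points with a severe loss of power. The documents do not support that: such gains within 30 days do not fit the 12-month build-up, and power for round 4 alone corresponds to no analysis that the plan describes. Nor do the documents show that the latrine comparison was contaminated.

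The objection does not remove the conflict between the printed rules. The article ties phase 2 to completion of CLTS, gives October for that, and dates a phase-1 round to November. It protects the final round explicitly but leaves round 4 unprotected. Following the Water intervention section as written would permit phase-2 work before the last phase-1 data are in.

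**Conclusion.** The point holds as a timing conflict. Phase-1 outcome data may be collected after phase 2 has opened, with an overlap of at most about one month. This rests on CLTS ending in October 2016 as printed and on phase 2 opening at that moment, as the Water intervention section says.

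The likely effect is small. At an assumed control gain of 10 %, about 0.7 points are lost at round 4 and about 0.2 points from the three-round average. That calculation covers early CLTS in control gotts only; an early water effect in the intervention arm would act the other way and is not quantified. The incidence sample size does not depend on November.

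The matter still deserves correction: the exposed round is one of three post-baseline primary rounds, and the safeguard costs almost nothing.

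**What to change.** Reconcile Study design, Primary endpoint, Water intervention, the sanitation-calendar section and Sanitary survey with one rule: no phase-2 activity, whether control-arm CLTS or water connection, starts in any gott of a kebelle until round 4 and the last calendar sheet have been collected in that kebelle. The kebelle is the natural unit because it is the randomization stratum and contains both arms.

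Record the date of the first phase-2 activity in each kebelle. If any calendar days fall after that date, leave them out of the phase-1 analysis for both arms of that kebelle, so that the comparison stays balanced within the stratum.

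The cost is a delay of up to a few weeks in phase 2, or the loss of at most one calendar month in affected kebelles.

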### Sanitation mapping

To assess the progress of latrine uptake, a sanitation map will be drawn and updated on a monthly basis. In addition to the households recruited for the longitudinal household survey, all the households in the 48 *gotts* will be registered to assess the real-time latrine status. All the households in the 48 *gotts* will be endowed with an identity number and marked with red, yellow, or green. If a household completes construction of an improved latrine, the WaSH promoter will mark that household in green on the sanitation map. If the latrine is under construction, that household will be marked in yellow. If the uptake of an improved latrine does not occur, the household will be marked in red on the sanitation map. Each WaSH promoter will present the sanitation map for his/her *gott* during a monthly review meeting of WaSH promoters, which is intended to stimulate healthy competition between the *gotts*. A system of evaluation and reward at the *gott* level is established, and this system is expected to create peer-pressure within the *gott*. WaSH promoters will educate *gott* residents on the herd immunity effects [19] of improved latrines and the importance of universal or sufficient coverage of improved latrines. If a *gott* reaches 80 % improved latrine coverage, it will be certified as a “healthy *gott*” by the local government and will be rewarded by the project team. Material rewards will be given to both WaSH promoters individually and to those *gotts* collectively that show fast progress in improved latrine uptake.

### Scoring latrine improvement status by household

For the assessment of improved latrine coverage in each *gott*, only the households with improved latrines will be counted. Households not practicing open defecation, but using communal or neighbor’s latrines will not be counted in the latrine coverage assessment. To avoid subjectivity of WaSH promoters in categorizing the real-time status of latrine uptake, photos will be taken of a latrine by WaSH promoters and will be assessed and scored by supervisors and the team leader.

Direct observation will be made, especially of the latrine construction, utilization, and open defecation status. As for the latrine status, we will not only observe the presence of latrines but will also assess the latrine type for categorization by each element (e.g., pit more than 2.5 m deep, slab, pit-hole cover, superstructure/wall, roof, door, and hand-washing facility within 3 m of the latrine). To evaluate latrine utilization, odor, a spider web at the entrance, fresh feces, and a worn path to the latrine will be observed. To evaluate for ongoing open defecation, the presence of human feces around the household compound and in the *gott* will be observed.

In addition, to avoid measurement errors, 3-m-long sticks marked every 50 cm will be provided to WaSH promoters to measure the pit-hole depth. The presence of wet feces around the pit-hole and a spider-web at the entrance, and a worn path to the latrine will be observed to assess latrine utilization.

